### Secondary response variables:

- Rate of **seroconversion** defined as the percentage of subjects with either a pre-vaccination MNT titer  $< 1:10$  and a post vaccination MNT titer  $\geq 1:80$  or a pre-vaccination MNT titer  $\geq 1:10$  and a minimum four-fold rise in post-vaccination HI antibody titer.
- Geometric mean titers at pre- and post-vaccination.
- Detectable increase in T cell (CD4+ and CD8+) responses against H5N1 virus specific antigens in avian influenza virus vaccinated individuals.
- Geometric mean antibody titers and detectable T responses against other pathogens and/or vaccines of interest in the target group of the avian influenza virus vaccine.

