## Seroprotection

Definition: The presence of a sufficiently high antiviral antibody levels expected to be associated with protection against a disease.

Measurement: Evaluation of anti-HA antibody levels post-vaccination to determine if they reach a protective threshold.

Significance: Seroprotection is expected if sufficiently high levels of antiviral antibodies are found in the sera of vaccinated individuals that likely gives protection against influenza disease. *Seroprotection rate* refers to the proportion of subjects in whom the level of anti-HA (or neutralizing) antibodies exceeds the value considered to be the limit of a significant level in terms of protection, e.g. the HI titer measured with the hemagglutination inhibition test (HI test)  $\geq 1:40$ . In addition to this, it is possible to evaluate the seroprotection as an increase in antibody concentration when the pre-vaccination sample is seropositive (e.g. HI titer  $>10$ ) and to estimate in how many of the study subjects the antibody (Ab) increase exceeds the factor considered as a critical response, a fourfold increase in the titer. In other words, if the pre-vaccination serum is negative, the postvaccination serum titer must be  $\geq 40$ ; if the pre-vaccination serum is positive, at least a fourfold increase in antibody titer is required.

According to the summary of product characteristics (SPC) of the currently marketed vaccine [3], based on the antibody responses elicited by the A/turkey/Turkey/1/2005 vaccine strain after two doses of AFLUNOV, a protective response may not be elicited in all recipients of the vaccine. According to previous research results presented in the SPC, the seroprotection rate against the homologous A/Vietnam/1194/2004 strain measured by the microneutralization (MN) test in adults aged 18-60 who received two doses of the vaccine was 67% (95% confidence interval 60–74) to 85% (78–90) and the seroconversion rate was 65% (58–72) to 83% (77–89). The seroprotection rate against the homologous A/turkey/Turkey/1/2005 strain measured with the MN test was 85% (79–90) and the seroconversion rate was 93% (89–96). Some cross-reactive immunity has been observed against H5N1 viruses from other clades. However, it is not known to what extent protection can be achieved against different H5N1 clade viruses. There is no immunological research data yet available for the avian influenza vaccine tailored against the A/Astrakhan/3212/2020 (H5N8) strain.

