## Secondary objectives

To evaluate

1. humoral immune responses produced by the avian influenza vaccine against different H5N1 development lineages (clades) that have occurred before 2023, or that are identified to occur during the study

2. cellular immune responses induced by the customized avian influenza vaccine, against different H5N1 clades
3. the effects of prior seasonal influenza vaccinations on the immune responses induced by the avian influenza vaccine
4. humoral immunity produced by seasonal influenza vaccinations against different H5N1 lineages evaluated from samples collected from healthcare personnel belonging to the target group of the seasonal influenza vaccine (“Immune responses to influenza vaccinations and viruses among health care personnel”, ClinicalTrials.gov Identifier: NCT03323112)
5. humoral and cellular immune responses induced by the H5N1 2.3.4.4b customized vaccine in subjects who have previously received avian influenza vaccines
6. humoral and cellular immune responses induced by other respiratory or non-respiratory pathogens and vaccines against them, and their potential association with immune responses induced by seasonal and avian influenza vaccines or viruses

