### Exploratory objective

Development of laboratory methods for influenza and avian influenza

**Primary outcome measure:** Seroconversion proportion in all study subjects 3 weeks after the second dose given at least 21 days after the first dose, as assessed by the microneutralization test.

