### Study hypothesis

It is expected that a two-dose avian influenza vaccination schedule will induce **seroprotection** in at least 70% of the vaccinees (the lower bound of the two-sided 95% CI for the percent of subjects achieving seroconversion meets or exceeds 70%). The criterion for seroprotection is titer value  $\geq 80$  as analyzed by microneutralization test (MNT).

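### The seroconversion definition mixes MNT and HI, and if MNT is meant throughout its two limbs do not meet at the 1:10 cut-off

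*Protocol*

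**What the plan says.** Three parts of the protocol bear on the rule.

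- **Secondary response variables** define seroconversion with two limbs: "defined as the percentage of subjects with either a pre-vaccination MNT titer" below 1:10 with a post-vaccination MNT of 1:80 or more; or a pre-vaccination MNT of 1:10 or more "and a minimum four-fold rise in post-vaccination HI antibody titer".
- **Primary outcome measure** (printed under Exploratory objective) is "Seroconversion proportion in all study subjects 3 weeks after the second dose", assessed by the microneutralization test. **Study hypothesis** adds "The criterion for seroprotection is titer value" 80 or more by MNT, and asks that the lower 95% confidence limit for the seroconversion percentage reach 70%.
- **Seroprotection** (Introduction) gives a general rule with HI as its example assay: "if the pre-vaccination serum is negative, the postvaccination serum titer must be" at least 40; "if the pre-vaccination serum is positive, at least a fourfold increase in antibody titer is required". Positivity is illustrated as an HI titre above 10.

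Secondary objective 3 is to evaluate "the effects of prior seasonal influenza vaccinations on the immune responses induced by the avian influenza vaccine". Objective 5 concerns responses in people vaccinated earlier against avian influenza. Neither names a comparison of seroconversion rates.

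**The concern.** There are two faults, one inside the other.

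First, the second limb changes assay midway. Subjects enter it on their MNT baseline and are judged on an HI rise, although the primary outcome is to be assessed by MNT. Laboratory methods treat HI as an additional assay that may be used depending on the virus lineage, so nothing ensures that paired HI titres will exist for these subjects.

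Second, the natural repair, replacing HI with MNT, does not make the rule coherent. In the Introduction the cut-off and the threshold fit together: four times 10 is the 40 asked of seronegative subjects. In the MNT rule the threshold is 80 but the cut-off is still 10, so the required titre halves on crossing the cut-off. Two subjects who both end at 1:40 are then classified differently, and the one with the larger rise fails.

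At stake is the primary proportion, since no other passage turns seroconversion into an MNT rule, and any description of seroconversion by vaccination history.

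**Working it through.** **Step 1. The plan's own figure.** Sample size inputs: p = 0.75, E = 0.05, Z = 1.96. n = 1.96² × 0.75 × 0.25 / 0.05² = 288.1, which agrees with the stated 288. The Wald lower limit at 75% is 0.75 − 1.96 × √(0.75 × 0.25 / n). This gives 0.69999 for n = 288 and 0.7010 for n = 300. The plan therefore sits almost exactly on its 70% criterion when the true rate is 75%.

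**Step 2. The bar at each baseline, reading HI as MNT.** The required post-vaccination titre is 80 if the baseline is below 10, otherwise 4 × baseline.

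| Baseline MNT | Post titre needed | Fold rise needed | Introduction's rule |
|---|---|---|---|
| <10 (coded 5, an assumption) | 80 | 16 | 40 |
| 10 | 40 | 4 | 40 |
| 20 | 80 | 4 | 80 |
| 40 | 160 | 4 | 160 |
| 80 | 320 | 4 | 320 |

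A change from <10 to 40 (eight-fold with the code 5) fails, while a change from 10 to 40 (four-fold) passes. In absolute titre the bar is lower only for baselines from 10 to below 20. The Introduction's rule has no drop anywhere.

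**Step 3. Comparison with a rule whose limbs meet** (post ≥80 and a four-fold rise, all in MNT).

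- Baseline <10: a four-fold rise needs less than 40, so 80 governs. Same result under both rules.
- Baseline 10 to <20: the present rule needs 4 × baseline, which is 40 to <80. The other rule needs 80. The present rule is easier.
- Baseline ≥20: 4 × baseline is at least 80. Same result under both rules.

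Every subject who passes the joined rule also passes the present one. The pooled proportion under the present rule is therefore equal or higher, never lower.

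**Step 4. Size, as illustration only.** The protocol gives no baseline titres and no titre SD. Assume post-vaccination titres are log-normal, with the same distribution at every baseline and P(≥80) = 0.75. Then P(≥40) = Φ(0.6745 + 1/SD), with SD in log2 units.

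| SD (assumed) | P(≥40) | Gain at baseline 10 |
|---|---|---|
| 1.2 | 0.934 | 18.4 points |
| 1.5 | 0.910 | 16.0 points |
| 2.0 | 0.880 | 13.0 points |

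The pooled rate is 0.75 + share × gain, with subjects in the band placed at exactly 10 and all others below 10. The lowest case is 0.75 + 0.05 × 0.130 = 0.7565. The highest is 0.75 + 0.20 × 0.184 = 0.787. So 5-20% in the band moves 75% to about 76-79%.

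**Step 5. What that does to the criterion.** With n = 300, a Wald lower limit of at least 70% needs 225 successes (224 gives 0.6975, 225 gives 0.7010). The binomial chance of 225 or more is about 53% at a true rate of 75%, 63% at 75.65% and 95% at 78.7%.

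**Step 6. Direction between groups.** Under the same model with SD 1.5, the pass probability at baselines <10 / 10 / 20 / 40 / 80 is 0.75 / 0.91 / 0.75 / 0.50 / 0.26. With SD 2.0 it is 0.75 / 0.88 / 0.75 / 0.57 / 0.37. If seropositive subjects were split equally between baselines 10 and 40, they would average (0.910 + 0.503)/2 = 0.71 or (0.880 + 0.569)/2 = 0.72, below the 0.75 of seronegative subjects. If instead the fold rise had the same distribution at every baseline, all seropositive subjects would pass with probability 0.95-0.98. The sign of a group difference is therefore not fixed.

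**The case against.** The strongest reply is that no MNT bar of 1:40 is written anywhere. The second limb says HI, so the gap belongs to a repaired text. That is right about the literal wording, and it is why the mixed assay comes first in this point. It does not save the rule: the literal text contradicts the MNT-assessed primary outcome, and the obvious repair carries the gap with it.

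A reader might infer that all baseline-positive subjects face an easier bar. In absolute titre that is untrue: the bar is equal at 1:20 and rises above it. It is true of every seropositive subject only on the fold-rise scale.

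A reader might also infer that objectives 3 and 5 are biased in favour of people vaccinated earlier. The protocol does not support this. It specifies no comparison of seroconversion rates there, gives no baseline titres, and also lists geometric mean titres and T-cell responses, which the cut-off does not touch. Step 6 shows that the sign can go either way.

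The share of subjects in the band may be small. The Introduction calls population immunity to avian influenza viruses low or absent and expects cross-reactivity from seasonal vaccination to be relatively short-lived. The Abstract puts seasonal vaccination in October-November 2023 and the start of avian vaccination in July 2024, and it calls the earlier avian vaccinees a small group. This stands, and it is why the 5-20% is illustrative. Finally, the protocol nowhere requires a positivity cut-off at a quarter of the seroprotective titre. That also stands, but the Introduction's own rule has this structure and the MNT rule lost it.

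**Conclusion.** The point holds in two parts. The firm part needs no assumption: the definition selects by MNT and judges by HI, against an MNT-assessed primary outcome, and the passages must be reconciled. The second part is conditional on MNT being meant throughout. The limbs then fail to meet, and subjects with baselines from 1:10 to below 1:20 can be counted as seroconverted at titres from 1:40 to below 1:80, short of the protocol's seroprotective level.

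Relative to a rule whose limbs meet, the effect on the pooled proportion has a known direction (up or none) but an unknown size. The 76-79% illustration rests on an assumed 5-20% share in the band, an assumed log2 SD of 1.2 to 2.0, and the same post-vaccination distribution at every baseline. Even 1 to 4 points matter where the criterion sits at the edge for a true rate of 75%. Descriptions by prior vaccination can be distorted if the groups differ in their share of subjects in the band. A direction for that distortion cannot be claimed.

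**What to change.** Define seroconversion in MNT throughout: post-vaccination MNT of at least 1:80 and at least a four-fold rise in MNT from baseline, for every subject. An equivalent form is a baseline below 1:20 with a post-vaccination titre of at least 1:80, or a baseline of at least 1:20 with a four-fold rise. This removes the assay mix, restores the structure of the Introduction's rule and ensures that no seroconverted subject falls below the seroprotective level. State in the Primary outcome measure that this is the definition used.

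The cost is a change of wording, with no added samples or assays. The seroconversion rate will be the same as, or slightly lower than, under the MNT-only reading of the present rule.

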by seasonal influenza vaccinations against different H5N1 clade viruses from serum samples collected from healthcare personnel belonging to the target group of the seasonal influenza vaccine as part of a separate clinical trial, where pre- and post-vaccination samples have been collected during each epidemic season since 2017 ("Immune Responses to influenza vaccinations and viruses among health care personnel", ClinicalTrials.gov Identifier: NCT03323112).

The distribution of seasonal influenza vaccines took place from October through November 2023, which was 1-3 months before the expected start of the distribution of avian influenza vaccines. In reality, due to delays in the licensure process, the avian influenza vaccination started only in July 2024. The avian influenza vaccine is given as a series of two doses. We will also evaluate whether receiving the seasonal influenza vaccine prior to the avian influenza vaccine, or the length of the interval between the vaccine doses influence vaccine-induced immune responses.

A small target group of laboratory personnel has previously been given avian influenza vaccines in 2009 and 2011 in Finland. Some of the individuals who previously received the vaccine are also included in the target group of the avian influenza vaccine that is now being distributed. One of the goals of this study is also to evaluate vaccine-induced responses against different virus lineages in persons who have previously received the avian influenza vaccine. We will also evaluate the cross-reactivity of antibodies, especially against the H5N1 2.3.4.4b clade, produced by the previous avian influenza vaccines from samples collected from these subjects previously, and at baseline for the current study.

For the analysis of the serum samples, we will use an in-house microneutralization test that we have developed and used in previous studies of avian influenza vaccine responses [5] and, depending on the virus clade under investigation, also the hemagglutination-inhibition (HI) assay. We will isolate peripheral blood monocytes and study vaccine induced cell-mediated immunity by analyzing the activation and persistence of avian influenza antigen induced T cell responses. Cross-recognition of T cell responses against different clade avian influenza viruses is also analyzed.

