In a previously published study, it was found that the seasonal influenza vaccine produced neutralizing antibodies also against H5N1 viruses in a large proportion of the subjects, indicating the

existence of an antibody-dependent cross-reactivity [7]. At one month after seasonal influenza vaccination, 28/38 (74%) showed a >4-fold increase of neutralizing antibody titer measured with neutralization test, and 13/38 serum samples (34%) showed a 20-fold increase of neutralizing Abs against influenza H5N1. HI titers against H5N1 remained at undetectable levels after seasonal vaccination in 13/38 (34.2%) of donors [7]. Also, H5N1 virus-specific CD4 T cell responses (in small frequency) were detected in several persons at baseline, and vaccination with a seasonal influenza enhanced the frequency of H5N1 specific CD4 T cells [7]. At 1 month after seasonal influenza vaccination influenza H5N1 specific CD4 response was detectable in 41.6% of study participants. Another study reported that vaccination with seasonal influenza vaccine provided a partial protection against a lethal H5N1 challenge in mice, and it was suggested that seasonal influenza vaccination could be used as an interim measure to decrease morbidity and mortality from H5N1 prior to the availability of a specific vaccine [8]. Mouse experiments have also shown that non-neutralizing antibodies against HA epitopes produced by multiple immunizations with seasonal influenza vaccines that are at least in part directed against conserved HA epitopes, mediated protection from challenge with H5N1 even in the absence of detectable neutralizing antibodies against the H5N1 virus [9]. Based on these findings, it is possible that partial cross-reactivity, potentially even some cross-protection may be achieved with the seasonal influenza vaccine through both neutralizing and non-neutralizing antibodies, and T-cell-mediated immunity, at least in some of the vaccinated. Since the concentration of serum antibodies remains at its highest for about three months after vaccination, and since the proportion of potentially cross-reacting antibodies is relatively small, it would be expected that the effect (cross-reactivity and possible cross-protection) may last a relatively shorter time after vaccination.

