### Assessment of humoral immunity against influenza

We will assess antibody-mediated immunity from serum samples using various methods. The most important serological assay is the microneutralization test (MNT), which measures the functionality of the antibodies and which we have used in previous studies of avian influenza vaccine responses [5]. In a previous study conducted by THL a MNT titer  $\geq 80$  was found to correspond to the value of the HI test  $\geq 405$ . Depending on the virus lineage under investigation, the functional activity of antibodies can also be assessed using the hemagglutination-inhibition (HI) assay. The concentration

of antigen-specific antibodies and antibody subclasses, as well as functional properties of the antibodies can be assessed with different methodologies.

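### The seroconversion rule judges baseline-positive subjects by a rise in HI titre, although the primary seroconversion outcome is to be assessed by microneutralization and HI is only conditional

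*Protocol*

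**What the plan says.** The primary outcome measure, printed under Exploratory objective, is "Seroconversion proportion in all study subjects", measured "3 weeks after the second dose given at least 21 days after the first dose, as assessed by the microneutralization test". That statement names the assay but sets no titre thresholds.

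Thresholds appear under Secondary response variables, where seroconversion is "defined as the percentage of subjects with either a pre-vaccination MNT titer" below 1:10 with a post-vaccination MNT titre of 1:80 or more, or a pre-vaccination MNT titre of 1:10 or more with "a minimum four-fold rise in post-vaccination HI antibody titer". The first limb uses MNT at both times. The second takes the baseline from MNT and the response from HI.

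On whether HI will be run, the Abstract lists it as "depending on the virus clade under investigation, also the hemagglutination-inhibition (HI) assay". Assessment of humoral immunity against influenza says: "Depending on the virus lineage under investigation, the functional activity of antibodies can also be assessed using the hemagglutination-inhibition (HI) assay". The same section ranks MNT as the main serological assay.

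**The concern.** The primary outcome promises an MNT assessment, but the rule needed to compute it sends one group of subjects to another assay. That group is foreseeable. Cohort 2, which lies inside cohort 1, consists of people who received H5N1 vaccine in 2009 and/or 2011. Seasonal vaccine has been recommended to the same target groups since September 2023, and the Introduction discusses cross-reactive antibody after seasonal vaccination.

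Two things are at stake. First, the pooled proportion tested against 70% would mix two assays, or would contain subjects without a result. Second, secondary objectives 3 and 5 concern prior seasonal and prior H5N1 vaccination. If those exposures raise baseline MNT, exposed subjects would more often be judged on HI and unexposed subjects on MNT, so the assay would be tied to the exposure under study.

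**Working it through.** **Step 1: the passages side by side.**

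| Place in the protocol | Baseline | Response | Assay status |
|---|---|---|---|
| Primary outcome measure | not specified | not specified | MNT |
| Secondary response variables, limb 1 | MNT below 1:10 | MNT 1:80 or more | MNT throughout |
| Secondary response variables, limb 2 | MNT 1:10 or more | four-fold rise in HI | mixed |
| Introduction, Seroprotection | negative or positive | 40 or more, or a four-fold rise | one scale; the examples are HI |
| Abstract; Assessment of humoral immunity | – | – | HI conditional on clade or lineage |

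The Introduction's two-branch rule does not mix assays, but its example values are HI values. The Seroconversion paragraph there is verbal only. No other rule gives MNT thresholds, so the primary outcome depends on the one under Secondary response variables.

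**Step 2: the plan's own sample size.** Inputs from Sample size: 95% confidence (Z = 1.96), p = 0.75, E = 0.05.

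n = Z² p(1 − p)/E² = 1.96² × 0.75 × 0.25 / 0.05² = 288.1. This matches the stated 288 (target 300). Changing the assay in limb 2 leaves these inputs, and so n, unchanged.

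**Step 3: slack around the criterion.** Study hypothesis asks for a lower 95% bound of at least 70% for seroconversion. The Wald lower bound is p − Z√(p(1 − p)/n).

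- n = 288, p = 0.75: 69.999%.
- n = 300, 225 converters (75%): 0.75 − 1.96 × 0.0250 = 70.1%.
- n = 300, 224 converters (74.67%): 0.7467 − 1.96 × 0.0251 = 69.7%.

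At the planning value, reclassifying one subject moves the result across the line.

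**Step 4: sensitivity, on assumed values.** The protocol gives no baseline-positive share and no HI-based conversion rate, so both are assumptions here. Baseline-negative subjects convert at 75% and n = 300. With share b and HI-based conversion h among baseline-positive subjects, the overall rate is (1 − b) × 0.75 + b × h.

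| b (subjects) | h | Overall | Lower bound |
|---|---|---|---|
| any | 75% | 75.0% | 70.1% |
| 2% (6) | 50% | 74.5% | 69.6% |
| 2% (6) | 100% | 75.5% | 70.6% |
| 5% (15) | 50% | 73.75% | 68.8% |
| 5% (15) | 100% | 76.25% | 71.4% |

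The shift can go either way. It is zero when HI and MNT classify alike.

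**The case against.** The strongest reply is that HI in limb 2 is a slip for MNT. The rule is listed as a secondary variable, the primary outcome fixes its own assay, and the Introduction's general rule stays on one scale. The protocol also does not say that HI will be omitted for the vaccine clade, and the affected group may be small: the Abstract describes the earlier H5N1 vaccinees as a small group, and the Introduction puts population immunity at little or none. All of this is fair and limits the size of the point. It does not remove the conflict, since a reader applying the printed rule would use HI.

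It is also fair that the tight bound in Step 3 is a feature of the design and is not caused by the assay mix. It shows only why a few classifications can matter.

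Three stronger inferences are tempting, and the documents do not support them.

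- *A mixed ratio biased toward non-conversion.* A reader might divide post-vaccination HI by pre-vaccination MNT and argue that, with HI about half of MNT, a true four-fold MNT rise shows as only two-fold. The natural reading is a rise from HI to HI, and there any constant factor k cancels: (k × post)/(k × pre) = post/pre, apart from detection limits. The halving also rests on reading the printed HI value of 405, set against MNT 80 in the laboratory section, as 40 followed by a citation number. That is plausible but an assumption, and matching one cut-off does not fix the relation over the whole range.
- *A loss of 7.5 to 15 points.* This would be 0.10 × 75% to 0.20 × 75%. The 10–20% share has no source in the protocol, and the product fails every baseline-positive converter. Even on the mixed ratio with HI = MNT/2, an eight-fold MNT rise gives 8/2 = 4 and passes.
- *Evidence that HI would fail here.* The Introduction reports that "HI titers against H5N1 remained at undetectable levels after seasonal vaccination in 13/38 (34.2%) of donors". That comes from a cited study of seasonal vaccination and says nothing about HI after the H5 vaccine in this trial.

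**Conclusion.** The point holds as an inconsistency in the definition on which the primary outcome depends. Subjects with a baseline MNT titre of 1:10 or more would be classified on an assay other than the one named for the outcome, and could not be classified if HI pairs are not run. The protocol fixes neither how many subjects are affected nor which way the proportion would move, and the effect is nil if the assays agree. It can still matter because, at an observed 75% with 300 subjects, the lower bound clears 70% by only 0.1 percentage point. That statement assumes a Wald interval and a true result near the planning value; a rate well above 75% would leave more room. The sample size stands.

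**What to change.** In the second limb of the seroconversion rule, replace HI antibody titer with MNT titer, and state that the pre- and post-vaccination titres come from the same assay against the same virus. Refer to this rule from the primary outcome measure, so that the outcome no longer borrows its definition by inference. If an HI-based seroconversion rate is also wanted, define it as a separate secondary variable with paired pre- and post-vaccination HI titres.

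The cost is a short wording amendment. MNT is already the assay named for the primary outcome and the samples are already planned, so no extra visit, sample or subject is needed. The change should be made before any titre is classified, because choosing the assay after seeing results could decide whether the 70% criterion is met.
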